### Statistical analysis

Patient characteristics will be compared and described by appropriate statistics. Data will be analyzed on an intention-to-treat basis. Normally distributed variables will be expressed by their mean and standard deviation and non-normally distributed variables will be expressed by their medians and 95% confidence levels. Categorical variables will be expressed as N (%). To test for normality, a D’Agostino and Pearson omnibus test will be performed [33]. Differences between groups will be tested by Student’s *t*-test for normally distributed data and Mann–Whitney *U*-test for not normally distributed data. Categorical variables will be compared with the Chi-square test or Fisher’s exact tests or when appropriate as relative risks. The difference of the primary effect variables will be analyzed using the Mann–Whitney *U*-test. The rate of freedom from ventilation will be analyzed according to the Kaplan-Meier method [34] and the results will be compared with the log-rank test hazard ratio’s are reported with 95% confidence limits. To take into account the stratification factors, we will perform an adjusted analysis. TBSA levels are group level data that will be included as a second level covariate in a multilevel linear regression model to assess the adjusted effect of our randomized treatment. Also the treatment effect on coagulation markers is investigated. Because they are clustered within each patient (repeated measurements) we will also use a multilevel model to evaluate the influence of the cluster effect on the model fit, that is we will compare the model fit without a second level (the patient) with the model fit that includes the patient as a second level. When appropriate, statistical uncertainty will be expressed by the 95% confidence levels. Statistical significance is considered to be at a *P* of 0.05. Analysis will be performed with SPSS version 18.1 (SPSS Inc., Chicago, IL, USA).

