### Randomization, blinding and intervention

Randomization is performed using ALEA® software (TenALEA consortium, Amsterdam, the Netherlands) and uses random blocks. Prior to randomization, patients are stratified for burn center and TBSA < 20% versus TBSA ≥ 20%. Patients are identified by study ID-numbers (randomization numbers) that are linked to the assigned study medication (heparin or normal saline). The pharmacist at each study site has access to the confidential file containing the randomization scheme, which links ID-numbers to appropriate ampoules. Since heparin and placebo are packed identically, they are provided with a temporary additional label ‘*verum*’ in case of heparin, or ‘placebo’ in case of saline. Before dispensing the medication to the ward, this additional label will be removed by the pharmacy, after which the medication is blinded for the study team. Nebulized volumes are identical.

Patients are randomly assigned to nebulization of study medication consisting of unfractionated sodium heparin (Pfizer, Melbourne, Australia) or sodium chloride 0.9% (Pfizer, Melbourne, Australia), administered every four hours (that is six times per day). For this, the total volume of identically packed 5 mL ampoules containing 25,000 IU of unfractionated heparin or 0.9% NaCl, is nebulized using an AeronebPro system (Aerogen Inc, Sunnyvale, CA, USA), connected to the ventilator circuit closest to the patient, but always in between the patient and the heat and moist exchanger if used. To prevent potential damage from nebulized heparin to the expiratory valve of the ventilator, a filter is placed in the expiratory limb of the circuit. Each nebulization session lasts 15 minutes. Nebulization of study medication is continued until tracheal extubation or death, but for a maximum duration of 14 days.

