### Follow-up

On the day of ICU admission, demographic and baseline data, as well as data on disease severity and extent of burn injury are collected. Data collection includes: gender, age, height, weight, functional status (independent, partially dependent or totally dependent), cardiac status (heart failure, according to the New York Heart Association (NYHA) [17], acute coronary syndrome *or* persistent ventricular tachyarrhythmia), alcohol status (in the past two weeks: 0 to 2 drinks/day, or more than 2 drinks/day), smoking status (in the past three months: never, former, or current). Data collection on relevant medical history include: COPD for which inhalation therapy or oral steroids are used, respiratory infection in the last month (upper or lower), history of active cancer, weight of loss more than 10% in the last six months, history of diabetes mellitus, chronic kidney disease, liver failure (Child-Pugh classification) [18], acquired immunodeficiency syndrome and use of relevant medications (including oral anti-diabetics, antibiotics in the last three months, statins, and corticosteroids). Regarding extent of burn injury, collected data include TBSA, partial or full thickness burn, Belgian Outcome in Burn Injury Study Group Index [19] and the Abbreviated Burn Severity Index (16).

Data on standard of care and clinical outcome variables (described below) are collected on a daily basis for the maximum duration of 28 days, until first discharge from ICU or death (whichever comes first). Data on length of stay in ICU and - hospital, mortality in ICU and hospital, and re-admissions to ICU are assessed on days 28 and 90 (Table 2).

**Table 2 T2:** Time schedule of study procedures

	**Day of admission (day 1)**	**Every day**^ **b/c** ^	**Days 1, 3, 5, 7, 9, 11 and 13**^ **c** ^	**Day of hospital discharge**	**Day 28**	**Day 90**
Screening and randomization						
screening^a^	X					
demographic data	X					
inclusion criteria	X					
exclusion criteria	X					
informed consent	X					
randomization	X					
Before start study medication						
blood sampling	X					
non directed broncho-alveolar lavage sampling	X					
Clinical procedures						
chest X-ray		X				
nebulization of study medication^c,d^		X				
blood sampling^c^			X			
non-directed broncho-alveolar lavage sampling^c^			X			
Clinical data collection						
%TBSA	X					
SAPS II	X					
Karnofsky score	X					
ABSI	X					
SOFA score		X				
LIS/OI		X				
ventilatory settings		X				

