### Statistical considerations

Sample size calculation - in a previous trial testing the efficacy of nebulized heparin, critically ill patients requiring ventilation for at least 48 hours showed a reduction of 4.6 days of ventilation (mean (SD) 22.6 (4.0) versus mean (SD) 18.0 (7.1)) [29]. We conservatively estimate that the improvement in burn patients with inhalation trauma is less than in a heterogeneous group of critically ill non-burn patients. We consider a reduction of three days of ventilation clinically relevant. We require 58 patients per treatment arm to observe a difference in the number of ventilator-free days at day 28 with (α < 0.05 at 80% power). Although burn patients with inhalation trauma usually have fewer ventilator-free days than critically ill non-burn patients, the standard deviation appears to be similar between burn injury patients [30] and critically ill patients in general [31], indicating that the sample size of 58 per arm for a total of 116 is sufficient to observe an improvement of three ventilator-free days (nQuery Advisor Software version 7.0, Statistical Solutions Ltd, Cork, Ireland).

Stratification - considering the fact that TBSA is associated with prolonged duration of ventilation [32], we want to avoid an uneven distribution of the severity of burns between study groups. Therefore, patients are stratified based on TBSA (≥ 20% versus < 20%). Provided that this stratification will only be used to ensure an equal distribution, and stratification is based on the median TBSA, it does not affect the sample size of this study.

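### The primary Mann–Whitney test is valid but uses no baseline covariate; adjusting for severity already recorded at admission could add a few points of power

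*Protocol article*

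**What the plan says.** All references are to the protocol article.

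- **Primary test** (Statistical analysis): "The difference of the primary effect variables will be analyzed using the Mann–Whitney" U-test. No covariate or stratum enters it.
- **Adjusted analysis** (same section): "To take into account the stratification factors, we will perform an adjusted analysis". The model is then described: "TBSA levels are group level data that will be included as a second level covariate in a multilevel linear regression model". No other covariate is named.
- **Strata** (Randomization, blinding and intervention): "Prior to randomization, patients are stratified for burn center and TBSA", with TBSA cut at 20%.
- **Why TBSA was chosen** (Statistical considerations, Stratification): "considering the fact that TBSA is associated with prolonged duration of ventilation". No correlation or explained variance is given.
- **Severity data** (Follow-up): "Regarding extent of burn injury, collected data include TBSA, partial or full thickness burn", and also the "Belgian Outcome in Burn Injury Study Group Index [19] and the Abbreviated Burn Severity Index". Table 2 lists %TBSA, SAPS II and ABSI in the column for the day of admission.

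**The concern.** The article treats burn extent as important enough to stratify on, then leaves it out of the primary comparison. The primary P value therefore gains no precision from the stratification or from the separate TBSA model. Two further severity scores, ABSI and SAPS II, are recorded at admission, and no sentence of the Statistical analysis section uses them.

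The stated sample size has no slack: 58 per arm gives almost exactly 80% power. If a baseline measure predicts ventilator-free days, leaving it out keeps explainable variation between patients in the error of the treatment comparison. At stake is a modest amount of power that data already being collected could supply.

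**Working it through.** **Inputs.** From Statistical considerations: a difference of 3 ventilator-free days, SDs of 4.0 and 7.1 from the earlier trial, 58 per arm, alpha 0.05 and 80% power. Sidedness is not stated; two-sided is assumed because it reproduces the stated number.

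**Step 1: reproduce the plan's figure.**
- Pooled SD = √((4.0² + 7.1²)/2) = √33.205 = 5.76.
- n per arm = 2 × (1.96 + 0.84)² × 33.205 / 3² ≈ 58, as stated.
- Power at 58 per arm = Φ(3 / (5.76 × √(2/58)) − 1.96) = Φ(2.80 − 1.96) = 80.1%.

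**Step 2: add a baseline covariate.** If it correlates ρ with the outcome, the residual SD is 5.76 × √(1 − ρ²). The article gives no ρ, so a range is shown.

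| ρ (assumed) | Explained variance ρ² | Power at 58 per arm |
|---|---|---|
| 0 | 0 | 80.1% |
| 0.30 | 0.09 | 83.6% |
| 0.36 | 0.13 | 85.2% |
| 0.40 | 0.16 | 86.4% |
| 0.50 | 0.25 | 89.9% |

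A gain of 5 points needs ρ of about 0.36. The formula ignores the degrees of freedom spent on covariates, so the figures are slightly generous.

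**Step 3: compare with a model that already holds TBSA levels.** Suppose TBSA levels explain 5% or 10% of the variance and the other measures add more (all assumed).

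| TBSA levels explain | Power with TBSA levels | Power if other measures add 5% / 10% / 20% |
|---|---|---|
| 5% | 82.0% | 84.0% / 86.0% / 89.9% |
| 10% | 84.0% | 86.0% / 88.0% / 91.8% |

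The increment is about 2 to 8 points. Because ABSI and TBSA probably overlap, the lower part of that range is more likely.

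**Step 4: try an outcome with many zeros.** A simulation (2,000 trials per setting, simple randomisation) assumed that about one third of controls die and score 0. The control mean was about 9.4 to 9.8 days, the SD about 9, and the true gain about 4.3 to 4.4 days.

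| Variance of the ranks explained by severity | Mann–Whitney | Rank analysis, severity split at the median | Rank analysis, continuous severity |
|---|---|---|---|
| about 0.11 | 77% | 80% | 81% |
| about 0.26 | 71% | 80% | 83% |

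With no true effect, rejection rates for these three analyses were 3.8% to 4.6%. Most of the gain comes from adjusting at all. Continuous rather than two-level severity adds 1 to 3 points.

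**Step 5: check against a larger SD.** At SD 9 and a 3-day difference, power is Φ(3 / (9 × √(2/58)) − 1.96) = 43% unadjusted. If covariates explain 20% of the variance it is 52%.

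**The case against.** The strongest reply is that nothing here is wrong. A Mann–Whitney test of a randomised comparison is valid, and the sample size was also computed without covariates, so the two agree. That stands. A reader might infer that the primary result would be biased, or that 58 per arm is miscalculated. Neither follows: the test's error rate already allows for chance imbalance, and the number reproduces.

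The gain also rests on a correlation that the article does not give. It supports prognostic value for TBSA only, and says nothing about how ABSI or SAPS II relate to ventilator-free days. The exclusions in Study population (TBSA above 60%, survival beyond 72 hours unlikely, expected ventilation under 24 hours) narrow the severity range and would tend to weaken any correlation. This stands too, and is why only a range can be offered.

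Three stronger readings are tempting and not supported:

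- **That death dominates the endpoint.** The one-third mortality in the Background is eventual mortality among burn patients with inhalation trauma in general. It is not 28-day mortality after this trial's exclusions.
- **That the TBSA split keeps only 2/π = 64% of the covariate's information.** That holds for a normally distributed covariate cut at its median. Here TBSA is capped at 60% and patients without skin burns are eligible. The article's remark about the median is conditional, and it does not define TBSA levels in the adjusted model as the two-level split.
- **That every admission score is safe to adjust for.** The part of Table 2 headed as preceding study medication lists only blood and lavage sampling. The table does not show that SAPS II is scored before the first nebulisation.

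It may also be said that the choice of covariates belongs in an analysis plan that is not shown. That does not dispose of the point, because the article itself fixes the primary test and names the covariate of the adjusted model.

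**Conclusion.** The point holds as an efficiency improvement. The primary test and the sample size are not in error. The primary comparison leaves out baseline severity that is already collected and that the article, for TBSA, regards as related to ventilation.

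On the SD of 5.76, adjustment would lift power from 80.1% to about 84% at ρ = 0.3 and about 86% at ρ = 0.4, and by less against a model already holding TBSA levels. These figures rest on assumed correlations, two-sided testing and a normal approximation. The lack of adjustment in the primary test matters more than how TBSA is coded.

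A reader might take adjustment as a remedy for the trial's power in general. It is not: at SD 9, power for three days would stay near one half even with 20% of the variance explained.

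**What to change.** Before unblinding, pre-specify the primary comparison of ventilator-free days as a covariate-adjusted rank analysis, for example rank ANCOVA. Use a small fixed set of covariates:

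- continuous %TBSA;
- one severity score, either ABSI, or SAPS II only if its values precede the first nebulisation;
- the randomisation strata, that is burn centre and TBSA below versus at or above 20%.

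Use continuous %TBSA in the adjusted regression model as well. Keep the unadjusted Mann–Whitney test as a sensitivity analysis.

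The cost is analysis wording, with no new data or patients. The effect is then reported as an adjusted rank contrast, which is less direct to read. With six centres entered as fixed effects, the model spends 5 + 1 + 1 + 1 = 8 degrees of freedom on covariates among 116 patients.

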## Background

Inhalation trauma adds to the morbidity and mortality of burn patients [1,2]. Indeed, up to one third of burn patients require hospitalization due to inhalation trauma and a substantial percentage of these patients develop respiratory insufficiency. Moreover, approximately one third of burn patients with inhalation trauma eventually die, markedly more than burn patients without pulmonary involvement.

The underlying pathophysiology of inhalation trauma is only partly understood. Injury is thought to be at least the result of heat exposure to the airway mucosa or inhalation of noxious particles or toxic gases [3]. Injury of airway mucosa could induce an inflammatory response resulting in vascular leakage and pulmonary edema [4]. Pulmonary cast-formation could certainly play a role, since one study of burn patients shows disturbed alveolar fibrin turnover [5], and several preclinical studies show obstructive airway casts after smoke inhalation [6-9].

At present, therapy for inhalation trauma is merely supportive [10]. Animal models of smoke injury [6,7,9] and clinical trials of burn patients with inhalation trauma suggest that local treatment with heparin has beneficial effects [11,12]. The objective of the present trial is to determine the clinical efficacy and safety of frequent nebulizations of heparin in burn patients with inhalation trauma. Furthermore, the present trial investigates local effects of heparin on pulmonary coagulation and inflammation.

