### Study population

Intubated and ventilated burn patients, > 18 years of age with bronchoscopically confirmed inhalation trauma are eligible for participation. Notably, intubated and ventilated patients without skin burns, but with bronchoscopically confirmed inhalation trauma, are also eligible for participation in HEPBURN.

Patients are excluded if they are not enrolled within the first 36 hours after trauma, if intubated and ventilated for longer than 24 hours prior to trial enrollment, and if unlikely to survive for more than 72 hours or have burns covering > 60% of total body surface area (TBSA). Patients are also excluded if the expected duration of intubation and ventilation is less than 24 hours. Other exclusion criteria are history of severe chronic obstructive pulmonary disease (COPD) with (non-invasive) ventilation or oxygen therapy at home or repeated systemic corticosteroid therapy for acute exacerbations, witnessed or bronchoscopically proven aspiration, any history of pulmonary hemorrhage in the past three months, any history of clinically important bleeding disorder, known allergy to heparin or heparin-induced thrombocytopenia, and pregnancy or breast feeding.

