### Study endpoints

The primary endpoint - is the number of ventilator-free days, defined as the number of days alive and breathing without the assistance of a ventilator during the first 28 days. Thus, a patient must be free of ventilation for 24 hours to have one ventilator-free day. If, after successful extubation the patient requires re-intubation and ventilation due to a surgical procedure, this episode will not count as a ventilator day. However, if after surgery, ventilation is prolonged due to respiratory insufficiency, the day(s) will be counted as ventilator days.

Secondary endpoints - are subdivided into clinical and laboratory outcome variables and safety variables. Clinical outcome variables include: (a) length of stay (ICU and hospital); (b) mortality (28- and 90-day); (c) mortality (ICU and hospital); (d) daily LIS; (e) daily OI; (f) daily SOFA scores; (g) cumulative dosages of sedatives; (h) incidence of VAP; (i) total number of bronchoscopy-guided cleanings of the larger airway. Laboratory outcome variables include: (a) levels of markers of coagulation and fibrinolysis in blood and lung lavage fluid, including but not limited to tissue factor, activated factor VII, antithrombin, thrombin-antithrombin complexes, activated protein C, plasminogen activator activity, tissue plasminogen activator, urokinase plasminogen activator, plasminogen activator inhibitor 1, fibrin degradation products and plasma levels of heparin; (b) levels of markers of inflammation in blood and lung lavage fluid, including but not limited to IL-1beta, IL-6, IL-8, IL-10, TNF-alpha, growth factors and markers of complement activation; and (c) biological markers of lung injury in blood and lung lavage fluid, including but not restricted to total protein, albumin and IgM, Clara Cell 16 protein and soluble receptor for advanced glycation endproducts. Safety variables include (a) occurrence of relevant bleedings - requiring surgery, requiring transfusion of clotting factors, requiring transfusion of blood products (red cells or platelets or plasma), any clinically important bleeding from the lung (prompting bronchoscopy); (b) any other transfusion of blood products - red cells or platelets or plasma; (c) confirmed HIT; and (d) prolonged activated partial thromboplastin time (aPTT > 150 seconds).

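### Freedom from ventilation is analysed by Kaplan-Meier and log-rank with no rule for deaths on the ventilator; under the usual censoring at death, the curve overstates the proportion liberated.

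*Protocol article*

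**What the plan says.** All places are in the protocol article.

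- **Statistical analysis**, on freedom from ventilation: "The rate of freedom from ventilation will be analyzed according to the Kaplan-Meier method [34"], and "the results will be compared with the log-rank test", with hazard ratios and 95% limits. No event or censoring rule for deaths is given.
- **Statistical analysis**, general rule for continuous variables: Student's t-test "for normally distributed data and Mann–Whitney *U*-test for not normally distributed data".
- **Study endpoints** lists "length of stay (ICU and hospital") as a secondary clinical outcome. The Statistical analysis section does not name it, so the general rule is the only one that could cover it.
- **Follow-up**: daily data are collected to day 28 at most, "until first discharge from ICU or death (whichever comes first"). Discharge and death close the daily record alike.
- **Background**: "approximately one third of burn patients with inhalation trauma eventually die".
- **Study population** excludes patients "unlikely to survive for more than 72 hours or have burns covering > 60% of total body surface area (TBSA"), so mortality in the trial may be lower than that.
- **Study endpoints** also defines the primary endpoint as days both alive and off the ventilator, and lists mortality (28-day, 90-day, ICU, hospital) separately.

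**The concern.** A patient who dies on the ventilator can never be liberated. Kaplan-Meier with that patient censored at death treats later liberation as still possible, at the rate seen in those who remain ventilated. One minus Kaplan-Meier then answers a hypothetical question (how many would be freed if nobody died), while a reader will take it as the proportion actually freed. In this population deaths are too common for the two to coincide.

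The log-rank test and hazard ratio computed in this way compare only the rate of liberation among patients still alive and ventilated. If one arm had more deaths and an unchanged weaning rate, fewer of its patients would come off the ventilator, yet the two curves would agree and the expected hazard ratio would be 1.0. The Discussion names serious bleeding as the main safety worry with nebulized heparin, so this pattern is one the trial has reason to look for.

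Length of stay raises a related question. If the dead are included with their time to death as the stay, an early death ranks as a short stay.

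**Working it through.** **The plan's own figures.** The article gives no expected liberation rate, no proportion dying on the ventilator and no figure for length of stay, so there is nothing on this point to reproduce. The stated sample size does reproduce: with a pooled SD of √((4.0² + 7.1²)/2) = 5.76 and a difference of 3 ventilator-free days, n = 2 × (1.960 + 0.842)² × 5.76² / 3² = 58 per arm. It rests on ventilator-free days and is not touched by what follows.

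**Assumed inputs.**
- Constant liberation hazard *l* of 0.06 or 0.08 per day (not in the article).
- Proportion dying on the ventilator by day 28: 10%, 20% or 33%. The top of this range borrows the one third from the Background, which is eventual mortality in a broader population. The lower values allow for the trial's exclusions and for deaths that occur later or off the ventilator.

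**Formulas.** With death hazard *d* on the ventilator:
- true proportion liberated by day 28 = l/(l+d) × (1 − exp(−28(l+d)));
- proportion dead on the ventilator by day 28 = d/(l+d) × (1 − exp(−28(l+d))), solved for *d*;
- one minus Kaplan-Meier with deaths censored = 1 − exp(−28·l).

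| l per day | Deaths on ventilator | d per day | Truly liberated | One minus Kaplan-Meier | Overstatement (points) |
|---|---|---|---|---|---|
| 0.06 | 10% | 0.0080 | 75.1% | 81.4% | 6.3 |
| 0.06 | 20% | 0.0175 | 68.6% | 81.4% | 12.8 |
| 0.06 | 33% | 0.0332 | 59.6% | 81.4% | 21.7 |
| 0.08 | 10% | 0.0098 | 81.9% | 89.4% | 7.5 |
| 0.08 | 20% | 0.0216 | 74.2% | 89.4% | 15.2 |
| 0.08 | 33% | 0.0415 | 63.7% | 89.4% | 25.7 |

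**Check with another parameterisation.** Fixing the proportion still ventilated at day 28 (5% to 20%) instead of the liberation hazard, with 10% to 33% deaths, gives an overstatement of 5.5 to 24 points.

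**Between arms.** Read the three rows at 0.06 per day as different arms. Moving from 20% to 33% deaths lowers true liberation from 68.6% to 59.6%, while one minus Kaplan-Meier stays at 81.4% and the liberation hazard ratio is 1.0.

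A simulation with 58 per arm (4,000 runs) shows what the test does. The control arm has 33% deaths and 10% still ventilated at day 28; the other arm has twice the death hazard and the same liberation hazard.
- True liberation falls from 57% to 44%; one minus Kaplan-Meier is 77% in both arms.
- Log-rank with deaths censored rejects in about 5% of trials, about 2.5% in each direction.
- Log-rank with the dead kept at risk to day 28 rejects against the worse arm in 22%.
- Mean ventilator-free days fall from 10.8 to 9.0, so the primary endpoint moves the right way.

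**Length of stay, conditional on the dead being included.** In the same simulation, ICU stay was taken as time to death or, otherwise, liberation plus 10 days (an assumption). The median falls from 15.8 to 12.2 days in the arm with more deaths, and Mann-Whitney calls that arm significantly shorter in 61% of trials. With a death hazard ratio of 1.5 the figure is 22%.

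**The case against.** **The article does not say that deaths are censored at death.** True. If the dead were carried as not liberated to day 28, one minus Kaplan-Meier would equal the cumulative incidence and the problem would vanish. A condensed article may also leave coding to the full protocol or analysis plan. But it does name the method, and without a further rule that method is usually run with censoring at death. The rule that would rescue it is the change requested here.

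**The log-rank test remains valid.** This stands. With deaths censored it is a proper test of the cause-specific liberation hazard. A reader might infer that the plan tilts the result towards heparin. It does not: a hazard ratio of 1.0 is a null result, and the simulated rejections split evenly. The error lies in reading the curve or the test as the chance of coming off the ventilator.

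**The length-of-stay part is inferred.** This also stands. The Statistical analysis section does not name that endpoint or say that the dead are included, so one cannot say that the plan counts early death as a good result, only that its general rule would allow it. The 61% depends on a doubled death hazard and an assumed stay after liberation.

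**Death is counted where it matters most.** Correct. Ventilator-free days require survival, mortality is a separate endpoint, and any death is within the interim safety comparison. Freedom from ventilation is not in the list of secondary endpoints and acts as support.

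**The top of the range is high.** Fair. One third is eventual mortality before this trial's exclusions, and the liberation hazards are assumed. At 10% deaths the overstatement is 6 to 8 points, smaller but still visible on a published curve.

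**Conclusion.** The point holds for the supportive analysis of freedom from ventilation. If deaths are censored in the usual way, one minus Kaplan-Meier overstates the proportion liberated by day 28 by about 6 to 8 points with 10% dying ventilated, and by about 13 to 26 points with 20% to 33%. These figures assume constant hazards and a liberation hazard of 0.06 to 0.08 per day. They describe the level of each curve, not a bias in the comparison of arms. The hazard ratio is cause-specific: it does not favour heparin, but it can fail to show that more deaths have left fewer patients liberated.

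For length of stay the conclusion is conditional: an early death counts as a short stay if the general test is applied with the dead included.

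The efficacy conclusion on ventilator-free days, the 58 per arm and the mortality endpoints do not depend on any of this. The change is worth making before analysis, but it does not threaten the trial's main result.

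**What to change.** State how deaths enter the analysis:

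1. Report the cumulative incidence of liberation to day 28 by arm, with death on the ventilator as a competing event. Compare arms with Gray's test or a subdistribution hazard ratio. With complete follow-up to day 28, the equivalent is to keep the dead at risk and censor them at day 28; ordinary Kaplan-Meier, log-rank and Cox procedures then give the intended quantities.
2. Keep the cause-specific hazard ratio alongside, labelled as the rate of liberation among patients alive and ventilated.
3. Analyse ICU and hospital length of stay as time to discharge alive in the same way, to day 28 and day 90.

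The cost is a few sentences in the analysis section and a recoded time variable. No new data are needed: the Follow-up section and its schedule of procedures (Table 2) already provide for daily ventilation status, length of stay, date of hospital discharge and date of death. The sample size is unchanged.

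### TBSA is wrongly called group-level data, burn centre is not named in the adjusted model, and the primary Mann–Whitney test uses neither randomisation factor, so it is valid but less efficient than it could be

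*Protocol article*

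**What the plan says.** All references are to the protocol article.

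- **Randomization, blinding and intervention:** "patients are stratified for burn center and TBSA", with TBSA cut at 20%. The Setting section lists six centres.
- **Statistical considerations (stratification paragraph):** TBSA is chosen because it is related to longer ventilation. The paragraph adds that "this stratification will only be used to ensure an equal distribution" and concludes that the sample size is unaffected.
- **Follow-up:** TBSA is among the burn-injury data collected for each patient.
- **Statistical analysis, primary test:** "The difference of the primary effect variables will be analyzed using the Mann–Whitney" U-test. No strata or covariates are mentioned.
- **Statistical analysis, adjusted analysis:** an adjusted analysis is announced to deal with the stratification factors, in the plural. The only model described for it is this: "TBSA levels are group level data that will be included as a second level covariate in a multilevel linear regression model". The second-level unit is not named, and neither is burn centre.
- **Discussion:** differences in care between centres are acknowledged as a possible confounder.

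**The concern.** There are two separate problems.

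First, the adjusted model as worded cannot be fitted sensibly. It puts a patient characteristic at the wrong level, and it names one of the two factors that it is meant to handle. An analyst following the text would have to guess what the model is.

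Second, stratified randomisation removes the between-stratum part of the outcome variance from the treatment comparison. A test that ignores the strata still counts that part as noise. Its P value is then too large on average, and some of the benefit of stratifying is lost. At stake is efficiency in a trial whose 58 patients per arm give almost exactly 80% power with no margin.

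**Working it through.** **1. At which level does TBSA sit?** Ventilator-free days give one value per patient, so in a two-level model the patient is level 1.

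- *If centre is the second level:* randomisation is stratified by TBSA class within centre, so the class differs between patients of the same centre. It is a level-1 covariate. A centre-average TBSA would be a true second-level covariate, but it is not the randomisation factor.
- *If the TBSA classes are the second level:* there are two units. A covariate with one value per class uses up the single degree of freedom between them, and none is left to estimate a between-class variance.

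Neither reading makes the sentence correct.

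**2. The plan's own sample size.** The inputs are a target of three days ("sufficient to observe an improvement of three ventilator-free days") and the earlier trial's "mean (SD) 22.6 (4.0) versus mean (SD) 18.0 (7.1"), with α 0.05 and power 80%. The SD used and the sidedness are not printed. I assume the pooled SD and a two-sided test, because they reproduce the stated figure.

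- Pooled SD = √((4.0² + 7.1²)/2) = 5.76
- n per arm = 2 × (5.76 × (1.960 + 0.842)/3)² = 57.9, rounded up to 58, as stated
- Power at 58 per arm: 80.1%

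**3. Effect of ignoring the strata (normal theory).** Let R² be the share of outcome variance explained by the randomisation factors. The documents give no value, so R² is an assumption. With 58 per arm, the SE used by the unadjusted test is 5.76 × √(2/58) = 1.07, and 3/1.07 = 2.80. Under balance within strata, the actual SE is smaller by the factor √(1 − R²). Therefore:

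- true size, unadjusted = 2 × (1 − Φ(1.96/√(1 − R²)))
- power, unadjusted = Φ((2.80 − 1.96)/√(1 − R²))
- power, adjusted = Φ(2.80/√(1 − R²) − 1.96)

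| Assumed R² | True size, unadjusted | Power, unadjusted | Power, adjusted | n per arm for 80%, adjusted |
|---|---|---|---|---|
| 0 | 5.0% | 80% | 80% | 58 |
| 0.05 | 4.4% | 81% | 82% | 56 |
| 0.10 | 3.9% | 81% | 84% | 53 |
| 0.20 | 2.8% | 83% | 88% | 47 |

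**4. Simulation with the rank tests themselves.** Setting: 116 patients, six equal centres by two TBSA classes, blocks of four, normal outcome, 4,000 runs per setting. The block size and the R² values are assumptions. The three right-hand columns give power for three days.

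| R² from TBSA + centre | Mann–Whitney size | Mann–Whitney | Rank regression, TBSA + centre | Van Elteren, 12 cells |
|---|---|---|---|---|
| 0 + 0 | 5.0% | 78% | 77% | 73% |
| 0.1 + 0 | 3.9% | 78% | 81% | 77% |
| 0.1 + 0.1 | 2.8% | 79% | 85% | 82% |

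In the last row, rank regression on TBSA alone has size 3.5% and power 82%, so it recovers only part of the loss. Stratifying on all 12 cells (116/12, about 10 patients per cell) costs power when the strata do not matter.

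**5. Bounded outcome.** Ventilator-free days are bounded at 0 and 28, so further simulations used log-normal ventilation times (log-SD 0.8) and a gain of about three days. Mortality and median ventilation time in the two TBSA classes are assumptions; none is in the documents.

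| Mortality; median days | R² | Mann–Whitney size | Mann–Whitney power | Van Elteren by TBSA, power |
|---|---|---|---|---|
| 18%/22%; 8/10 | about 2% | 4.6% | 57% | 58% |
| 15%/25%; 7/11 | about 7% | 4.3% | 57% | 60% |
| 10%/30%; 6/13 | 20–25% | 2.4% | 51% | 62% |

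The gain runs from about 1 to 11 points, depending on an unknown. The absolute power is 57% even where the strata hardly matter. It therefore reflects mainly the assumed spread of the outcome, not the neglect of the strata.

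**The case against.** - **The plain test is valid.** This stands. Type I error is not inflated. On the plan's own sizing, power with the unadjusted test is 80% or slightly more for every R² shown in step 3. A reader might infer that leaving out the strata invalidates the primary analysis or pushes the trial below its planned 80%. The documents support neither. The loss is relative to a better test.
- **Centre may be intended.** The plural wording and the multilevel structure suggest that centre could be the unnamed second level, and a condensed article need not list every model term. A reader might conclude that centre has been left out of the analysis; the text shows only that it is not named. TBSA would be at the wrong level even if centre is meant.
- **TBSA may be second-level in another model.** For the repeated coagulation markers the patient is the second level, and there a patient's TBSA would belong at that level. However, the TBSA sentence concerns the adjusted treatment effect and comes before the markers are introduced.
- **The TBSA effect may be weak.** Burns above 60% TBSA are excluded, and re-intubation for surgery does not count as ventilator time. Both could weaken the association, which is why R² has to be shown as a range.
- **No estimate in days?** A reader might infer that the plan cannot judge its three-day target. The rank test alone gives no such estimate, but the linear model does.
- **Stratification is said not to affect the sample size.** That statement concerns the number of patients, not the analysis, and does not resolve the point.

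**Conclusion.** The description of TBSA as group-level data is wrong as written, and the adjusted model does not name one of the two factors that it promises to handle. This rests on the text alone.

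The efficiency point holds in direction, because the protocol itself says that TBSA is related to ventilation time. Its size is conditional. Under normal theory with the pooled SD of 5.76 and balance within strata, R² of 0.1 to 0.2 means a true size of 3.9% to 2.8% and a shortfall of about 3 to 5 power points against an adjusted test. At R² = 0 there is no shortfall. No single power figure for this trial can be attached to the omission, since any such figure depends on mortality and ventilation times that the documents do not give.

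This is a correction of the supporting model and a recommended gain in efficiency.

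**What to change.** 1. **Primary test.** Use a rank-based test that accounts for the randomisation factors. The preferred form is a rank or ordinal regression adjusted additively for TBSA class and centre. A van Elteren test by TBSA class is simpler, but leaves the centre variance in the error. Do not stratify on all 12 cells.
2. **Sensitivity analysis.** Keep the plain Mann–Whitney test in this role.
3. **Adjusted linear model.** State TBSA class as a patient-level fixed covariate, and centre as the second level or, as there are only six centres, as a fixed effect.
4. **Reporting.** Give the adjusted difference in ventilator-free days with a 95% CI beside the primary test, so that the three-day target can be judged.

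The cost is analysis wording only, to be settled before unblinding, since TBSA and centre are already recorded. If the strata turn out not to be prognostic, additive adjustment costs a few degrees of freedom (77% against 78% power in the simulation at R² = 0).
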